**Fig. 1 Fig1:**
[figure not shown]
Research design and planned timeline of the DCAT study

### Study setting

The study takes place in the Friedland transit camp “Grenzdurchgangslager Friedland”. The camp was established in 1945 in the middle of Germany, Lower Saxony. Since its foundation, it has received over 4 million people. Nowadays, it accommodates two groups of refugees: resettlement refugees (who have already gone through the refugee-status determination process) and asylum seekers (who have applied for asylum after arrival in Germany and are waiting for the decision regarding their refugee-status). Currently, there are 200–400 resettlement refugees and asylum seekers mainly from the middle east and north Africa countries [23]. The primary healthcare centre in Friedland is an outpatient clinic staffed by a team of six GPs offering medical consultations to refugees and asylum seekers during weekdays. These doctors work in co-operation with nursing staff from Malteser International, which also operates the facility outside regular consultation hours [24].

According to the Services for Asylum Seekers Act (AsylBLG sections 4 and 6) [2], only primary healthcare services for acute medical conditions are insured [11]. These conditions represent diseases and complaints commonly examined by primary healthcare doctors (medical emergencies, acute conditions, pregnancy and vaccinations) [25].

### The digital communication assistance tool (DCAT) concept

The digital communication assistance tool, which will be implemented and evaluated in the study, was developed by aidminutes GmbH, a former study group at Leuphana University in Lüneburg and the Department of General Practice at the Göttingen University Medical Centre.

DCAT is able to collect medical histories in 13 different languages/dialects (Modern Standard Arabic, Arabic Syrian, Arabic Egyptian, Arabic Tunisian, Arabic Moroccan, Turkish, Persian, Kurdish Sorani, Kurdish Kurmanji, Kurdish Feyli, Pashto Kandahari, Pashto Mazurka) and generate a translated summary in German for the German-speaking doctors (see Figs. 2 and 3).

**Fig. 2 Fig2:**
[figure not shown]
Available languages in the DCAT

**Fig. 3 Fig3:**
[figure not shown]
Main signs and symptoms window of DCAT displayed in Arabic

The questioning structures are partly based on the concept of “programmed diagnostics in general medicine” by Braun and Mader [14], a cybernetic approach for gaining information on common signs and symptoms as well as diagnostic procedures. Several GPs with significant experience in the medical care of migrants have developed the DCAT medical history algorithm and overseen the whole programming process. Professional interpreters translated the DCAT content in its entirety. Using DCAT, the patient is asked to specify a symptom (e.g. a headache) or concern (e.g. prescription of a medication). It is possible to include additional symptoms and order them by importance. At the same time, the symptoms input can be elaborated on through further inquiry and via the possibility of visual information.

### Study population

#### Participants and inclusion criteria

In this study, informed participants can use DCAT:At the primary healthcare centre for patients seeking medical care andAt the social service bureau referral point.

All patients who meet the following inclusion criteria are eligible to participate in the study:Patients who speak one of the following languages: Arabic, Kurdish, Turkish, Persian, Pashto or any of the following dialects: Modern Standard Arabic (MSA), Arabic Syrian, Arabic Egyptian, Arabic Tunisian, Arabic Moroccan, Kurdish Sorani, Kurdish Kurmanji, Kurdish Feyli, Pashto Kandahari, Pashto Mazurka.The patients (or in case of children their parents) provide written informed consent before participating in the DCAT study.

### Recruitment and informed consent

Participating in the study and utilising DCAT is voluntary. Written informed consent is collected from each patient (or from the parents for patients under 18 years) willing to participate before using DCAT. All participants have the right to withdraw from the study at any point and all their collected information is immediately deleted.

Since the DCAT study is restricted to non-German-speaking patients, who might also have difficulties in reading and writing, audio- and visual content in the chosen language has been incorporated into DCAT [15, 16].

The potential participants are informed of the DCAT study directly on their arrival in Friedland camp through interpreters and social service workers. There are also posters and flyers (available in different languages) describing DCAT distributed across various sites in Friedland. Due to the structure of the referral system in Friedland, which mandates that asylum seekers need to get a permit from the responsible social service worker before being referred to the primary healthcare centre, we also included the social service bureau as a recruiting location in this study (see Fig. 4).

**Fig. 4 Fig4:**
[figure not shown]
DCAT study procedures and implementation process

### Sample size calculation

The sample size calculation is based on the average numbers of patients in the last 12 months in Friedland. Due to fluctuations in refugee flows (ranging from 285 to 636/month), it is difficult to predict how many patients will be treated at the primary healthcare centre during the study period and meet the inclusion criteria, especially regarding the available languages. Despite these uncertainties, during the six months recruitment period we aim to include a total sample size of 880 participants (study group: 440 patients using DCAT, 440 patients not using DCAT). The sample size calculation is based on the consultation rates for medical treatment at the primary healthcare centre in Friedland as this is the primary outcome of the study protocol. Our previous research in the preparation phase revealed an average consultation rate for medical treatment of 2.65 (SD: 3.44) consultations per patient. Assuming a 10% dropout rate, to measure a minimal difference of 0.65 consultations per patient, 5% significance (two-sided) and a standard deviation of 3.5, 20 patients should be recruited per week to use DCAT to achieve the identified sample target.

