**Methods:**

The study aims to monitor the implementation of a new digital communication assistance tool (DCAT) and to investigate its impact on the mutual understanding between refugee patients and their German general practitioners (GPs). In the first study phase, an action-oriented approach is used to implement DCAT. In the second study phase, DCAT use will be evaluated with a mixed methods design.

The main outcome assesses the re-consultation rates of patients before and after using DCAT. Secondary outcomes include the usability of the tool, its acceptance and perceived quality by patients, the accuracy of the information collected as determined from analysing the reasons for the consultation (ICPC-2 codes), and diagnosis (ICD-10 codes). The acceptance by patients, socio-demographic factors and native language are also taken into account.

The research designs for both study phases include questionnaires, semi-structured interviews, non-participant observation and analysis of collected patients’ data.

All the collected data is pseudonymised.

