## Methods

### Design

The first study phase follows an action-oriented approach, meaning that observation outcomes can be used as an input to improve the content and implementation process of DCAT. This pragmatic approach allows us to make adjustments within a complex intervention in a barely known field, in response to unexpected problems and new opportunities that arise throughout the study. In contrast to other interventional procedures, the action research method requires close collaboration between researchers and other involved parties in the field [14, 15]. This approach also has proved its validity in evaluating health-related issues among refugees and asylum seekers [16, 17]. The “action” follows a circular process consisting of planning, implementation, observation and reflection, which is repeated several times. Since it is not possible to ascertain which challenges may be faced during the testing, it is difficult to determine ahead of time the duration of the action research method. This initial study phase ends with a successful three week preliminary testing with patients supported by intensive field observation and technical backup. Following this testing, the final version of DCAT will be fixed and will remain unchanged during the second study phase.

For a better understanding of DCAT impact, potential and limitations, a mixed methods research design is to be combined with quantitative and qualitative research methods in the second study phase [18, 19]. The quantitative approach includes DCAT-users and non-DCAT users and therefore offers the possibility to compare both groups in an interventional study design.

The primary outcome will be the consultation rate of patients who used DCAT compared with those who did not use this digital translation tool. As we found in a previous pilot study, the consultation rate of refugee patients at the primary healthcare centre is higher, especially compared to the non-refugee population, and this might be a result of miscommunication. Also, consultation rates are key values for healthcare costs.

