### Study measurements

#### Quantitative measurements

**Mode and frequency of consultation**

Every presentation of patients in the primary healthcare centre is registered through a coding system that depicts the time of the consultation as well as the condition presenting (e.g., medical treatment during consultation hours, medical emergency). Re-consultations of patients in the primary healthcare centre will also be recorded.

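### The primary outcome counts consultations per patient with no start, stop or time at risk, so any difference in camp stay between DCAT users and non-users is mixed with the DCAT effect

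*Protocol article*

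**What the plan says.** The Design section of the protocol article defines the outcome: "The primary outcome will be the consultation rate of patients who used DCAT compared with those who did not use this digital translation tool". The abstract words it differently: "The main outcome assesses the re-consultation rates of patients before and after using DCAT". Neither gives an observation period.

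The only unit appears under Sample size calculation, where the preparation-phase figure is an "average consultation rate for medical treatment of 2.65 (SD: 3.44) consultations per patient" and the aim is "to measure a minimal difference of 0.65 consultations per patient". The six months mentioned there are a recruitment period, not follow-up per patient.

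Under Study setting, the site is a transit camp for "resettlement refugees (who have already gone through the refugee-status determination process) and asylum seekers", the latter still awaiting a decision. Under Recruitment and informed consent, taking part and using DCAT are voluntary.

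Visits are "registered through a coding system that depicts the time of the consultation" (Mode and frequency of consultation). Language, age, nationality, asylum status and sex are also obtained. Arrival date, departure date and length of stay are not listed. The Data analysis section says that the two groups' differences will be tested for significance and mentions no exposure time.

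**The concern.** A count per person is a rate only when everyone is observed for the same time, or when the time is in the denominator. In a transit camp a patient who leaves early has fewer chances to return to the clinic. A comparison of mean counts then reads a short stay as few consultations.

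Nothing in the design balances stay between the groups:

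- Users select themselves.
- Asylum seekers need a social-service permit before referral, and the social service bureau was made a recruiting site for that reason. Recruitment route is therefore tied to asylum status, which is a plausible determinant of stay.
- Patients who stay longer have more visits at which they could become users.

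Shorter stays among users would imitate a benefit, and longer stays would hide one. The abstract's before-and-after wording does not escape this, because periods of unequal length before and after use have the same fault.

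At stake is whether the primary result can be interpreted. If departure dates are not captured, a later analysis plan cannot supply the missing denominator.

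**Working it through.** **Inputs from Sample size calculation.** Mean 2.65; target difference 0.65; "5% significance (two-sided) and a standard deviation of 3.5"; 440 per group; "Assuming a 10% dropout rate". Power is not stated, so 80% is assumed here.

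**The plan's own figure.** n per group = 2 × (1.96 + 0.842)² × SD² / 0.65².

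- SD 3.5: 456 per group, and 456 / 0.90 = 507 after dropout. The stated 440 is not reproduced.
- SD 3.44 with no dropout: 440.

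This mismatch is a separate matter. Below, 440 is taken as stated, and 440 × 0.90 = 396 is used for completers.

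**Standard error.** SE = 3.5 × √(2/440) = 0.236; at 396 per group, 3.5 × √(2/396) = 0.249.

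**Shift from stay alone.** Assume no DCAT effect and visits strictly proportional to time in camp. A relative difference x in mean stay then shifts the mean by d = 2.65x. The chance of a significant result is

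P = 1 − Φ(1.96 − d/SE) + Φ(−1.96 − d/SE).

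For x = 10%: d = 0.265, d/SE = 1.12, P = 0.20.

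| Difference in mean stay | Shift d | P at 440 per group | P at 396 per group |
|---|---|---|---|
| 5% | 0.13 | 9% | 8% |
| 10% | 0.27 | 20% | 19% |
| 15% | 0.40 | 39% | 36% |
| 20% | 0.53 | 61% | 57% |
| 24.5% | 0.65 | 79% | 74% |

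The nominal level is 5%. The last row is the stay difference that yields the whole target: 0.65 / 2.65 = 24.5%. An observed difference of 1.96 × 0.236 = 0.46, or 17% of 2.65, is already significant at 440 per group.

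**If visits are less than proportional to stay.** If only half of the visits scale with stay, d is halved. A 10% stay difference then shifts the mean by 0.13 (about 9% rejection), and a 20% difference by 0.27 (about 20%).

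**What is not known.** The article gives no stay lengths, for all patients or by group. The values of x and the proportionality are assumptions.

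**The case against.** The strongest reply is that this is an absence in a condensed article. A follow-up period may stand in the full protocol or in the timeline and procedure figures, which are not shown, and an exposure offset is the sort of detail left to an analysis plan. That stands as a caution. However, the period over which a count is taken is part of the outcome definition and decides which data are collected. The text that defines, sizes and analyses the outcome uses a per-patient unit and refers to no window.

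A second reply is that total consultations per patient is a legitimate quantity, because the Design section also justifies the outcome by healthcare cost. This stands in part. The same section attributes the high rate to possible miscommunication, and on that question time in camp is a nuisance.

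Third, the camp clinic deals mainly with acute conditions, pregnancy and vaccinations, so visits may cluster soon after arrival. This stands: the bias would then be smaller than in the table.

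Three stronger readings are tempting but not supported:

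- A reader might infer that stay does differ by DCAT use. The article gives no stay data, so this is a risk of unknown size.
- A reader might infer that patients enrolled late are observed for less time. No passage says that counting ends with recruitment, and the Discussion speaks of an initial 18-month study period. Truncation would also bias the comparison only if enrolment dates differed between the groups.
- A reader might take an SD of 3.44 on a mean of 2.65 as evidence of varying exposure. Differing morbidity produces the same overdispersion. Because the planning SD rests on the site's own per-patient data, any such variation is already in the sample size.

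**Conclusion.** The point holds in conditional form. As written, the primary comparison cannot separate fewer consultations from less time in camp, and neither the group formation nor the listed measurements protect against a difference in stay. If stay differs between users and non-users, the result is biased, and the direction cannot be told from the article.

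With full proportionality, no true effect and SD 3.5, false rejection at 440 per group runs from about 9% for a 5% stay difference to about 79% for 24.5%, where the shift equals the planned effect. These figures show sensitivity and are not an estimate of the actual bias. The matter should be corrected because the remedy is cheap and the departure date must be collected prospectively to be sure of having it.

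**What to change.** - **Define the window.** Start counting at the same defined point in both groups, for example the index consultation. Stop at camp departure or at a pre-specified common cut-off.
- **Record the departure date for every patient.** This is needed with a fixed window too. Without it, someone who leaves before the window ends still counts as a low consulter.
- **Analyse person-time.** Compare re-consultations with a count model that has a log(days at risk) offset, adjusted for the asylum status already collected.
- **Close data collection late enough.** Keep it open for one full window after the last enrolment.
- **Restate the planning figures.** The 2.65, the 0.65 and the SD are per patient over an unstated period. Re-express them on the new scale and derive the sample size again. That needs stay data which the article does not give.

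The cost is one administrative date per patient, a short wait after the last enrolment, restated planning figures, and the loss of visits after the cut-off from the primary count. Visit times are already registered and camp identity cards already carry the study code, so little new infrastructure should be needed.

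### The stated 440 patients per group does not follow from the stated SD of 3.5 and 10% dropout at 80% power or higher, and the achieved power depends on an unstated meaning of 440

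*Protocol article*

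**What the plan says.** Everything is in one paragraph of the protocol article, under Sample size calculation.

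- **Target:** "we aim to include a total sample size of 880 participants (study group: 440 patients using DCAT, 440 patients not using DCAT"), to be reached in a six-month recruitment period.
- **Background data:** the preparation phase found an "average consultation rate for medical treatment of 2.65 (SD: 3.44) consultations per patient".
- **Planning inputs:** "Assuming a 10% dropout rate, to measure a minimal difference of 0.65 consultations per patient, 5% significance (two-sided) and a standard deviation of 3.5".
- **Recruitment:** the sentence with the planning inputs ends by concluding that 20 DCAT users per week are needed to reach the target.

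Two SDs therefore appear: 3.44 as an observed value and 3.5 as the planning value. No power is given. The text does not say whether 440 is counted before or after dropout.

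**The concern.** The paragraph prints both the inputs and the result, so the result can be checked. With the planning SD of 3.5 it comes out too small at 80% power, even before dropout is added. With the other SD, 3.44, and no dropout, it comes out exactly. This suggests that the number was computed from one set of inputs and described with another.

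At stake is what the primary comparison of consultation rates can show. If recruitment closes at 880 and the true power for 0.65 is below the level readers will assume, a null result may be read as stronger evidence against a 0.65 difference than it is. It is also unclear whether recruitment should end at 440 per group or continue until 440 per group can be analysed.

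**Working it through.** **Inputs (protocol article, Sample size calculation):** difference 0.65; two-sided 5%; planning SD 3.5; observed SD 3.44; dropout 10%; 440 per group; 20 DCAT users per week; six months, taken as 26 weeks. **Assumption:** 80% power, because none is stated.

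**Formula**, two independent means with equal groups, normal approximation: n per group = 2 × (1.960 + 0.842)² × SD² / 0.65².

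**Step 1. Reproduce 440.** With SD 3.44, 2 × 7.849 × 11.83 / 0.4225 = 439.7, which rounds up to 440. This contains no dropout allowance. With 10% dropout it becomes 440 / 0.9 = 489.

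**Step 2. Use the stated planning SD.** With SD 3.5, 2 × 7.849 × 12.25 / 0.4225 = 455.1, so 456 evaluable per group. With dropout, 456 / 0.9 = 506.7, so about 507 enrolled per group (1,014 in total). At 90% power the figures are 610 evaluable and 678 enrolled.

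| SD | Power | Evaluable per group | Enrolled per group, 10% dropout |
|---|---|---|---|
| 3.44 | 80% | 440 | 489 |
| 3.5 | 80% | 456 | 507 |
| 3.5 | 90% | 610 | 678 |

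**Step 3. Look for a power at which the stated inputs do give 440.** With SD 3.5 and 10% dropout, 74% power gives 437 enrolled and 75% gives 448. A power of about 73 to 75% therefore reproduces 440 within 3%.

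**Step 4. Power that 440 delivers at SD 3.5.** Power is approximately Φ(0.65 / (3.5 × √(2/n)) − 1.960).

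- 440 enrolled with 10% lost in both groups: n = 440 × 0.9 = 396. Power = Φ(2.613 − 1.960) = 74.3% (74.2% with the noncentral t).
- 440 evaluable: power = Φ(2.755 − 1.960) = 78.7% (78.6% with the noncentral t).

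**Step 5. Difference detectable with 80% power at SD 3.5:** 2.802 × 3.5 × √(2/n). For n = 396 this is 0.70; for n = 440 it is 0.66.

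**Step 6. Weekly rate.** 20 × 26 = 520 DCAT users, or 468 after 10% dropout. The rates implied by the candidate targets are:

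- 440 enrolled: 440 / 26 = 16.9 per week
- 440 evaluable: 489 / 26 = 18.8 per week
- 456 evaluable: 507 / 26 = 19.5 per week

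A rounded 20 per week is compatible with either of the last two.

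**The case against.** The best defence rests on the grammar of the planning sentence. Dropout appears there as an input to the weekly rate, and the rate serves a target already named. On that reading 440 is the number to be analysed, and the 10% loss is covered by over-recruiting: 440 / 0.9 / 26 = 18.8 per week, rounded up to 20. What remains is a gap of 16 patients per group (456 against 440, 3.6%), of the size one would expect if the calculation used 3.44 and the text rounded it to 3.5. Power is then about 79%.

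This defence is reasonable, and it rules out three stronger statements that a reader might infer:

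- **That 880 patients give 74% power as a matter of fact.** This requires 440 to mean enrolled and 10% to be lost in both groups. The verb in "we aim to include a total sample size of 880 participants (study group: 440 patients using DCAT, 440 patients not using DCAT") favours enrolment but does not settle it. Dropout is mentioned only alongside the recruitment of DCAT users. With loss in that group alone (396 against 440), power would be about 76%.
- **That 440 can arise only from SD 3.44, 80% power and no dropout.** Step 3 shows another route, at about 73 to 75% power. That would be an unusual choice to leave unsaid, but the article does not exclude it.
- **That the weekly rate contradicts the target.** It does so if 440 is the enrolment figure, but not if 440 is the evaluable figure.

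It may also be said that the power could stand in a fuller protocol. That is fair, and its absence here is not the finding. At 80% power or any higher value, the printed inputs do not give the printed result, and neither reading of 440 removes the gap.

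**Conclusion.** The point holds in a limited form. The figure of 440 per group does not follow from a difference of 0.65, SD 3.5, two-sided 5% and 10% dropout at 80% power or higher. It coincides with the preparation-phase SD of 3.44 at 80% power without dropout.

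Against the stated inputs at 80% power, the shortfall is 16 per group if 440 is evaluable (456 − 440) and 67 per group if it is enrolled (507 − 440). Power for 0.65 lies between about 74% and 79%, depending on which is meant. On the milder reading the loss is small; on the other it is about 6 percentage points on the primary outcome. This is a moderate correction of stated figures.

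The conclusion assumes that 80% was the intended power, which the exact match at SD 3.44 supports but does not prove. It also assumes a comparison of two means with equal groups and, for the 74%, equal loss in both groups.

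**What to change.** Use one SD throughout the paragraph, state the power, and say whether 440 counts patients enrolled or evaluable. Then take one of two routes.

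1. **Keep 880 and restate what it delivers at SD 3.5.** If 440 is enrolled and losses are equal: 396 evaluable per group, about 74% power for 0.65, and 80% power for 0.70. If 440 is evaluable: about 79% power for 0.65, 80% power for 0.66, and about 489 enrolled per group. The cost is a change of wording and a slightly lower stated power. The 396 and 74% should not be printed unless 440 is confirmed as the enrolment figure.
2. **Set the target at 456 evaluable and about 507 enrolled per group**, with 80% power stated. In the DCAT group, 20 per week over 26 weeks (520) already covers this. The paragraph gives no weekly rate for patients not using DCAT, so the authors should confirm that the same number can be reached there.

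In either case, show the weekly rate as the chosen enrolment figure divided by the number of recruitment weeks, so that the target and the rate agree.
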